### Study design/plan

The study will be conducted as a multicenter, randomized, double-blind, placebo-controlled, parallel, phase 2, proof-of-concept study, a collaboration between the Department of Neurology, Odense University Hospital, the Danish Pain Research Center, Aarhus University, and the Department of Neurology, Aarhus University Hospital. The study comprises a 1-week baseline period and a 12-week treatment period followed by a 3-week period including a tapering down and follow-up period (Fig. 3). Patients should have an average intensity of pain of at least 4 (NRS scale) and not above 9 in the baseline period, but this is not revealed to the patient. Before inclusion, the diagnosis of probable or confirmed neuropathic pain will be confirmed by the investigator using a detailed pain history, focused clinical and neurological examination, and evaluation of previous paraclinical examinations.

**Fig. 3 Fig3:**
[figure not shown]
Study design. Blue arrows, visits; red arrows, telephone calls. IN irritable nociceptor, NIN non-irritable nociceptor, QST quantitative sensory testing, R randomization, V visit

At screening, QST will be performed according to the standard practice and a standard protocol [15]. QST will be used to categorize patients as having either the irritable or the non-irritable nociceptor phenotype [5]. QST will be done by a nurse not otherwise involved in the study, and the investigators and study nurses involved in the study will be blinded to the results of the QST and the phenotype of the patients. The patients are not informed about their pain phenotype and its expected impact on pain relief, and thus the exact definition of irritable nociceptor phenotype is provided only in the study protocol submitted to the ethical committee. Trial participants and all personnel involved in the study are blinded to assignment to interventions.

At the screening, patients will be trained in reporting pain intensity accurately, using cases to improve the patients’ understanding of the numeric rating scale (NRS) and how to score their average daily pain.

### Study drugs

The trial medication will be supplied from the pharmacy at Odense University Hospital (Sygehus Apotek Fyn). Lacosamide (50 mg) and identical placebo are given as capsules and taken orally twice a day. We have adapted a slow titration in an attempt to increase tolerability and reduce dropout. Patient will start with 50 mg bid followed by a 6-week titration phase, increasing the dose by 50 mg weekly to 150 mg bid in week 5 with an increase to 200 mg bid in week 6. The maximal dose is 400 mg/day (200 mg bid), and the dose is kept constant from week 6 until the end of the treatment period. If patients experience intolerable side effects, they are permitted to lower the dose to the highest tolerable dose, but not lower than 100 mg bid. After the treatment, the patients will have a 1-week tapering-down period, following which they will continue in the study for another 2 weeks. This is done to assess whether the pain returns to baseline values, which is relevant in order to understand possible placebo responses. The allowed escape medicine for any type of pain during all of the study periods is paracetamol, up to 4000 mg daily, and the intake is noted in a diary.

### Study population

Patients with peripheral neuropathic pain will be recruited from the Department of Neurology, Odense University Hospital, the Pain and Headache Clinic, Department of Neurology, Aarhus University Hospital, other departments, and via advertisements. Patients with peripheral neuropathic pain following peripheral nerve injury (including amputation), painful polyneuropathy, postherpetic neuralgia, and painful radiculopathy will be included. Patients with central neuropathic pain (e.g. pain due to stroke, multiple sclerosis, and spinal cord injury) will not be included. Patients with trigeminal neuralgia, which is sometimes partly a central neuropathic pain and has different treatment recommendations, will also not be included. Patients with CRPS type I or II will not be included.

#### Inclusion criteria

Age ≥ 18 yearsVerified probable or definite peripheral neuropathic pain for at least 3 months [16]Average pain intensity of at least 4 and not above 9 on an 11-point (0–10) NRS during the 7-day baseline weekWritten informed consent (Additional file 2)

#### Exclusion criteria

Other causes of pain in the same area or other concomitant pain that cannot be distinguished from the neuropathic painPatients who cannot cooperate or are expected not to be able to complete the project and patients who do not speak DanishKnown and current cardiac conduction disturbance (2° or 3° atrioventricular (AV) block, prolonged QTc interval > 450 ms, heart rate < 50 or > 110 bpm, QRS interval > 120 ms (ECG required)), significant cardiac, renal, or liver disease, or other severe illness; sitting diastolic blood pressure below 50 mmHg or above 105 mmHg; in patients treated with pregabalin, also PQ interval > 0.2 sMajor depressive episode within 6 months, recurrent depressive disorder or other significant psychiatric disease, and alcohol, illicit drug or drug abusePregnancy or lactationWoman of childbearing potential, unless they use acceptable effective contraception as defined in the Clinical Trials Facilitation Group (CTFG) during the study and at least 2 weeks after, or if their male partner has had a vasectomy and is their sole partner; a negative pregnancy test is required; acceptable effective contraception is defined in the CTFG (http://www.hma.eu/fileadmin/dateien/Human_Medicines/01-About_HMA/Working_Groups/CTFG/2014_09_HMA_CTFG_Contraception.pdf)Known allergy to lacosamide or excipientsConcomitant pain treatment with tricyclic antidepressants, topical analgesics (lidocaine, capsaicin), lamotrigine, oxcarbazepine, cannabinoids, or strong opioids that cannot be discontinued; other treatments for neuropathic pain are allowed in a stable dose (from 14 days before randomization to completion of the trial) if they cannot be tapered off completelyConcomitant treatment with products known to be associated with PQ (PR) prolongation other than pregabalinPatients inappropriate for placebo treatmentPlanned surgeryUse of sodium channel blockers within at least five half-lives and investigational drugs within 30 daysPatients on a controlled sodium diet unless the amount of sodium in the capsules is acceptable for their dietThe score “yes” on item 4 or item 5 of the Suicidal Ideation section of the Columbia Suicide Severity Rating Scale, if the ideation occurred in the past 6 months, or “yes” on any item of the Suicidal Behavior section, except for the “Non-suicidal Self Injurious Behavior” if this behavior occurred in the past 2 years

### Pain diary

Patients will keep a diary in which they will record their daily average pain score as assessed on the NRS (0–10) from the baseline week before treatment, throughout the treatment period and for another 3 weeks. The diary will be electronic (or, in some cases, on paper). The patients will also record their daily intake of study medication during the treatment period and their use of escape medication (number of tablets). The investigators will on a regular basis check that the diary is filled out during the treatment period, and daily during the first and last weeks to avoid missing data.

### Randomization

Randomization to the two treatments is done after the baseline period, by the pharmacy, using a computer-generated randomization list using block sizes unknown to the investigators. The patients will be stratified into two groups: patients with and without the irritable nociceptor phenotype. Allocation concealment will be ensured, as the randomization code will not be released until after the phenotype has been established and patients are randomized consecutively. The code for randomization will be stored in the pharmacy until the study is completed. Both sites receive for each randomization code a sealed envelope with information on the treatment given. The code envelope is only unsealed/opened in emergency cases if the safety of the patient requires knowledge of the randomization code.

### Compliance

In the pain diary, patients are required to record their intake of study medication morning and evening. Residual capsules shall be returned at the end of the treatment period (visit 3). The number is compared with the daily records of consumption of capsules in the dairy and the number of returned capsules is also recorded on the case report form. Furthermore, patients are contacted via telephone at least once during the treatment period and interviewed in a standardized manner to ensure compliance.

## Outcomes

### Primary outcome

The difference in the mean value of the patients’ daily ratings of average pain intensity in the baseline week and the last week during treatment as experienced during the past 24 h rated on an 11-point numeric rating scale (NRS; 0 = no pain, 10 = worst possible pain)

### Secondary outcomes

Pain relief (complete, good, moderate, mild, none, worse pain) (visit 3)Use (average numbers of tablets and number of subjects taking any dose) of escape medication (paracetamol) during the treatment period

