Lacosamide is a functionalized amino acid molecule, developed as an antiepileptic drug. It selectively enhances the slow inactivation of voltage-gated sodium channels and interacts with the collapsin-response mediator protein-2 (CRMP-2), which is involved in neurotrophic pathways [8]. Lacosamide is efficacious in animal models of neuropathic pain [9]. In humans, the effect of lacosamide on neuropathic pain is inconclusive, based on inconsistent results and very large placebo responses (i.e. a large reduction in pain intensity during placebo treatment) in the few randomized controlled trials (RCTs) [2, 10–13]. Improvements were seen for secondary variables such as sleep, patient global impression of change (PGIC), quality of life, and pain interference; and two trials with multiple dosing showed efficacy of lacosamide 400 mg on the primary outcome [11, 12]. Recently, a study in patients with SCNA9A-associated painful small-fiber polyneuropathy has been carried out [14]. These studies did not reveal serious or clinically relevant safety issues, and the majority of reported adverse events (most commonly dizziness, nausea, and headache) were mild to moderate. Previous lacosamide trials have not used patient stratification or looked for predictors. The aim of this study is therefore to assess whether specific pain phenotypes based on sensory testing are linked to an increased response to lacosamide in patients with peripheral neuropathic pain.

Standard Protocol Items: Recommendations for Interventional Trials (SPIRIT) were used in writing this manuscript (see Fig. 1 and Additional file 1).

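### The escape-medication outcome takes no account of baseline-week paracetamol use, so pre-existing differences between the non-randomised phenotype groups would be read as differences in response

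*Protocol article*

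**What the plan says.** The Secondary outcomes section of the Protocol article names two outcomes. One is pain relief; the other is "Use (average numbers of tablets and number of subjects taking any dose) of escape medication (paracetamol) during the treatment period". On the period, Study design/plan states: "The study comprises a 1-week baseline period and a 12-week treatment period". On the indication, Study drugs states: "The allowed escape medicine for any type of pain during all of the study periods is paracetamol". That section adds that intake is noted in a diary, so baseline-week use is recorded. The Pain diary section describes the entry as a number of tablets and mentions no reason for use.

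The primary outcome is built differently. Primary outcome and Statistics define it as the change in mean pain from the baseline week to the last seven treatment days.

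The primary objective compares patients with and without the irritable nociceptor phenotype on lacosamide. Exploratory objectives moves the secondary outcomes to the total population only if no phenotype difference is found, so the phenotype comparison comes first for them too. Statistics assigns the Mann–Whitney test to secondary outcomes and Fisher's exact test to dichotomous data.

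**The concern.** Patients are randomised to lacosamide or placebo within phenotype, but nobody is randomised to a phenotype. A raw on-treatment count therefore mixes two things: how much paracetamol each group used before the trial drug, and how much the drug changed that use. The primary outcome deals with this by taking a change from baseline; the escape-medication outcome does not.

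If one phenotype group habitually takes more paracetamol, for its neuropathic pain or for another complaint, it would appear to respond less well. The outcome could then contradict or falsely support the primary result. Background makes other use plausible, since it says of earlier lacosamide trials that "the majority of reported adverse events (most commonly dizziness, nausea, and headache) were mild to moderate". The exclusion criteria also admit patients with other pain that can be told apart from the neuropathic pain.

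**Working it through.** **Inputs.** Baseline is 7 days and treatment is 12 weeks, or 84 days (Study design/plan). Each phenotype has 54 patients randomised 2:1 (Statistics), so 54 × 2/3 = 36 on lacosamide and 18 on placebo. The document gives no paracetamol use rate, no headache rate by arm and no power for this outcome. There is no plan figure to reproduce, and the rates and correlations below are assumptions.

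**1. Carry-over of baseline use.** Let the two phenotype groups use b1 and b2 tablets per day at baseline, with d = b1 − b2, and let lacosamide lower use by the same amount e in both.
- Raw comparison: (b1 − e) − (b2 − e) = d.
- Change from baseline: (−e) − (−e) = 0.

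The raw outcome shows d although the response is identical. Between lacosamide and placebo, randomisation makes the expected d zero, so there is no bias.

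**2. Precision.** Let baseline and on-treatment use have equal standard deviation s and correlation r. The variance is s² for the raw value, 2s²(1 − r) for the change, and s²(1 − r²) after regression on baseline. Regression subtracts r·d, so (1 − r)·d remains.

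| r (assumed) | Raw variance | Change variance | Adjusted variance | d left: raw / change / adjusted |
|---|---|---|---|---|
| 0.3 | 1.00 s² | 1.40 s² | 0.91 s² | 1 / 0 / 0.7 |
| 0.5 | 1.00 s² | 1.00 s² | 0.75 s² | 1 / 0 / 0.5 |
| 0.7 | 1.00 s² | 0.60 s² | 0.51 s² | 1 / 0 / 0.3 |

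The change removes d fully but is noisier than the raw value when r is below 0.5. Adjustment always gains precision but removes only part of d.

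**3. Any dose over 12 weeks.** With weekly use probability p and independent weeks, the share of users is 1 − (1 − p)^12. With within-patient correlation ρ it is 1 − B(a, b + 12)/B(a, b), where B is the beta function, a = p(1/ρ − 1) and b = (1 − p)(1/ρ − 1).

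| Weekly use p | Independent | ρ = 0.3 | ρ = 0.5 | ρ = 0.7 |
|---|---|---|---|---|
| 5% | 46% | 21% | 15% | 10% |
| 10% | 72% | 38% | 27% | 19% |
| 20% | 93% | 63% | 48% | 36% |
| 30% | 99% | 79% | 64% | 50% |
| 50% | 100% | 94% | 84% | 72% |

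Exact power of Fisher's test at the 5% level, 36 against 36:

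| Weekly use | Last week only | 12 weeks, independent | 12 weeks, ρ = 0.3 | 12 weeks, ρ = 0.5 |
|---|---|---|---|---|
| 10% v 30% | 0.47 | 0.90 | 0.91 | 0.83 |
| 20% v 50% | 0.70 | 0.03 | 0.88 | 0.87 |
| 30% v 60% | 0.64 | 0.00 | 0.54 | 0.69 |

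Neither window is better throughout.

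**4. Titration inside the window.** Study drugs describes the steps as "increasing the dose by 50 mg weekly to 150 mg bid in week 5 with an increase to 200 mg bid in week 6", from a start of 50 mg twice daily. Reading the weekly step as 50 mg per day, which reproduces the stated week-5 dose, 100 mg bid is reached in week 3. Weeks 1–5 are below the maximal dose: 5/12 = 42%. Only weeks 1–2 are below the 100 mg bid that defines the per-protocol population: 2/12 = 17%.

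**The case against.** Whole-period paracetamol use is a legitimate measure of total analgesic need, and a window that differs from the primary outcome's is not an error. Statistics says no baseline differences between phenotypes are expected. The outcome is secondary, carries no power claim, and an analysis plan not shown may already correct for baseline. The first point stands, and it is why the whole-period figure should be kept. The second is an expectation and does not mention paracetamol; pain is still analysed as a change under the same expectation. On the third, the article itself fixes the outcome as a treatment-period count; if the analysis plan corrects for baseline, the point is met.

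A reader might infer four stronger criticisms, which the document does not support:
- **The any-dose part is bound to hit a ceiling and carries almost no information.** With independent days and one common daily probability of 1%, 2% or 5%, 1 − (1 − q)^84 gives 57%, 82% or 99% users, against 7%, 13% or 30% over 7 days. Paracetamol use probably clusters in the same patients, and step 3 shows that the ceiling then often disappears. Average tablets has no such ceiling.
- **The outcome is biased against lacosamide through headache.** Background names headache but gives no excess over placebo. In the phenotype comparison both groups take lacosamide, so headache adds noise unless it differs by phenotype.
- **Use for other pain cannot be separated at all.** Safety has adverse events recorded in the diary, with onset and termination times, so use that coincides with a reported headache can be examined.
- **Titration dilutes 42% of the window.** That takes the maximal dose as the benchmark; against the per-protocol floor it is 17%.

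**Conclusion.** The point holds as a weakness of the outcome definition. A raw treatment-period count compared between non-randomised phenotype groups carries any pre-existing difference in paracetamol use into the result one for one. In the lacosamide-placebo comparison the cost is precision only. The size in tablets cannot be given, because the document states no use rates.

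The one-for-one result assumes an additive, equal response. If the drug lowers use proportionally, or many patients take none at baseline, a change score corrects imperfectly. Other-cause use adds noise; bias from headache and a ceiling on any dose are possibilities that depend on unstated rates. The primary analysis is unaffected, but the correction is cheap enough to be worth making.

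**What to change.** Define the secondary outcome as the change in mean daily paracetamol tablets from the baseline week, or adjust for baseline use, and choose between the two before unblinding. The change suits the phenotype comparison and the planned Mann–Whitney test. Adjustment suits the lacosamide-placebo comparison but needs a regression model that the article does not plan. Report the last treatment week, matching the primary outcome, alongside the whole-period figure and not in its place. Give the any-dose count for the baseline week, the last week and the whole period. Optionally, add a diary tick for the reason of use if the full protocol has none. Leave the permitted escape use as it is.

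The cost is slightly more analysis, a noisier 7-day summary, and added noise in the change score if baseline and on-treatment use are only weakly correlated. The optional tick adds a small diary burden; everything else uses data already planned.

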### Tertiary outcomes

The Patient Global Impression of Change (PCIG) measures the patients’ overall change (all aspects of general health) from baseline on a 7-point scale (very much improved, much improved, minimally improved, no change, minimally worse, much worse, very much worse) (visit 3)Pain impact on activities, sleep, and mood (NRS 0–10, from no impact to worst impact possible) (visit 2 and 3)Mean values of the daily pain ratings for the other 11 weeksPresence of 30% and 50% reduction of pain (from pain diary, baseline vs. last week of treatment)Symptoms of depression and anxiety and sleep disturbance assessed using the Patient-Reported Outcome Measurement Information System (PROMIS), the PROMIS questionnaire asks about symptoms experienced during the previous 7 days with a frequency or severity grading of symptoms; the scores are converted into PROMIS *T* scores, which are standardized relative to an American/US reference population, and to categories of impairment (normal and mild, moderate, and severe impairment) [16] (visits 2 and 3)The intensity of pain symptoms assessed by the Neuropathic Pain Symptom Inventory (NPSI) [7] (visits 2 and 3)Mechanical allodynia is assessed by brushing a soft brush (Somedic) twice with a speed of 1–2 cm/s and cold allodynia is assessed twice by a 20 °C cold thermal roller (Somedic); pinprick hyperalgesia is assessed using a pinprick stimulator as the difference in pain score (two stimulations at a control and at the pain side); pain is rated on the NRS (0–10) (visits 2 and 3)Hyperpathia assessed by repetitive mechanical pinprick stimulation at a rate of 2 Hz for 60 s and pain on the NRS (0–10) at 10-s intervals until the evoked pain has ceased [17] (visits 2 and 3)Nerve excitability testing is performed on the (nonaffected) wrist (visits 2 and 3)

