## Background

Neuropathic pain is a common pain condition that has a major negative impact on health-related quality of life [1]. Despite many years of intensive research into the prevention and management of this pain condition, it remains difficult to treat. Evidence-based recommendations list three drug classes as first-line therapies: tricyclic antidepressants (TCAs), α2δ calcium channel ligands (gabapentin and pregabalin), and serotonin and noradrenaline re-uptake inhibitors (SNRIs) (duloxetine, and venlafaxine) [2]. However, many patients are left with no or limited pain relief using these drugs in maximum tolerated doses or drug combinations. There is therefore an urgent need for other drugs for treating neuropathic pain. There is increasing interest in identifying predictive biomarkers associated with a specific tractable pain mechanism linked to a drug with a known mechanism of action [3, 4]. One promising approach is to use quantitative sensory testing (QST), which involves standardized mechanical and thermal stimuli to assess loss (negative signs) and gain (positive signs) of sensory function. In a phenotype-stratified randomized, double-blind, placebo-controlled study, our research group has recently shown that the sodium channel blocker oxcarbazepine reduced pain more in patients with the so-called irritable nociceptor phenotype than in patients without this phenotype [5]. In addition, a malfunctioning descending pain modulation (e.g. assessed by the conditioned pain modulation (CPM) test) [6] and patient-reported outcomes assessed with validated questionnaires such as the Neuropathic Pain Symptom Inventory (NPSI) may represent predictive biomarkers for drug efficacy [7].

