### Statistics

With a minimally relevant between-phenotype group difference in total pain reduction of 1.25 NRS points, a standard deviation of 1.6 within phenotype groups [5], 80% power, and a 5% risk of type I error, the sample size estimate is 27 + 27 patients for the primary objective. With a minimally relevant treatment versus placebo difference in total pain reduction of 1.5 NRS points, 80% power, and a 5% risk of type I error, the sample size estimate is 30 + 15 patients using a treatment:placebo ratio of 2:1 for the supportive objective. With an expected dropout rate of 1/6 (data available for intention-to-treat (ITT) analysis), the recruitment stops when 54 patients in each phenotype group have been randomized to lacosamide and placebo in a 2:1 ratio. Thus, we expect to randomize 108 patients. For the explorative outcome in case there is no phenotype difference, 72 patients randomized to lacosamide and 36 patients randomized to placebo in the total population in an ITT population will give > 90% power to find a minimally relevant treatment versus placebo difference in total pain reduction of 1.25 NRS points and 85% power to find a minimally relevant treatment versus placebo difference in total pain reduction of 1.0 NRS points.

Statistical analysis of the primary outcome will be performed by *t* test and of the secondary outcomes by the Mann–Whitney *U* test. Nondichotomous tertiary outcomes will be performed by *t* test or Mann–Whitney *U* test, where applicable. Since we do not expect differences in baseline between the two phenotypes [5], a major impact of baseline pain intensity on the outcome, or a center effect, we do not plan to include these as covariates in the analyses.

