For the primary outcome, the delta values from the average pain intensity in the baseline week to the last treatment week (last 7 days) will be used. Response rates and other dichotomous data are analyzed using Fisher’s exact test. For the primary (and supportive) objective, we are interested in the mechanistic aspects and in understanding whether the sensory phenotype “irritable nociceptor” is a prognostic biomarker for a sodium channel blocker in therapeutic doses. Therefore, the primary analysis for the primary objective is the PP population. Missing data will not be replaced. The PP population comprises those patients who complete at least 2 weeks on stable medication with at least 100 mg bid. Thus, if patients who fulfil the PP definition stop the treatment before the 12th week, the last seven pain scores on stable medication will be used for the primary analysis, and they will be invited for an additional visit identical to visit 3. All patients who have taken at least one study capsule will be encouraged to stay in the study, complete the diary, and come for a visit after 12 weeks.

As a secondary analysis, the ITT population will be used. The ITT analysis will also be used for the explorative outcome in the whole population if there is no phenotype difference. Given a substantial dose-dependent withdrawal rate due to adverse events, the EMA suggests a conservative responder analysis and that noncompleters are defined as nonresponders [19]. Therefore, the baseline observation carried forward (BOCF) in the ITT population (all patients randomized) will be the primary imputation method, and the last observation carried forward (LOCF) will be done as a secondary imputation method. Patients will be asked to complete the pain diaries despite their withdrawal from trial medication to minimize the need for imputation.

Significance is considered at the 5% level. If there are changes to the original statistical plan, the type of change and the date of change will be documented, and the document will be signed by the sponsor.

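### Evoked-pain tertiary outcomes: the stated reason for omitting covariates does not carry over to them, and an unadjusted irritable v non-irritable comparison could show a difference without any phenotype-specific effect (minor)

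*Protocol article*

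**What the plan says.** **Outcomes.** Protocol article, Tertiary outcomes: pain on brushing, pain on a cold roller, pinprick hyperalgesia and hyperpathia are rated on the 0–10 NRS at visits 2 and 3. The pinprick measure contrasts two body sites: "pinprick hyperalgesia is assessed using a pinprick stimulator as the difference in pain score", taken at a control side and at the painful side.

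**Test.** Statistics: "Nondichotomous tertiary outcomes will be performed by" t test or Mann–Whitney U test, as applicable. Covariates are declined with the reason "Since we do not expect differences in baseline between the two phenotypes [5", together with no expected major influence of baseline pain intensity and no expected centre effect. The covariates named are baseline pain intensity and centre; baseline evoked pain is not mentioned. "Significance is considered at the 5% level".

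**Phenotype.** Study design/plan: "QST will be used to categorize patients as having either the irritable or the non-irritable nociceptor phenotype". The Background describes QST as using "standardized mechanical and thermal stimuli to assess loss (negative signs) and gain (positive signs) of sensory function". The exact definition is deliberately kept out of the article. Exploratory objectives lists preserved thermal sensation and gain of sensation as QST features to examine, without saying that they define the phenotype.

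**Contrasts.** The primary objective compares average pain change between phenotypes on lacosamide, which is not a randomised comparison. The supportive objective compares lacosamide with placebo in each phenotype. For the evoked-pain outcomes the article names neither the contrast nor whether change or the visit-3 value is tested.

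**The concern.** Equal baselines are plausible for diary-rated average pain. They are much less plausible for bedside brush, cold and pinprick responses if patients were sorted by QST partly on gain of sensation. The group labelled irritable would then contain more patients with the sign at visit 2. A patient who scores 0 for brush or cold pain cannot improve. A decline that is proportionally the same in everyone, whether from drug, placebo response or time, therefore produces a larger absolute fall where the sign is more common. The Background reports very large placebo responses in earlier trials of this drug, so a shared decline is realistic.

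These measures lie close to the mechanistic question. The Discussion says that the trial is not powered for a difference in drug–placebo effect between phenotypes and must rely on supportive evidence. An unadjusted phenotype difference in evoked-pain change could be read as such support when it reflects only different starting points.

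**Working it through.** **Plan's own figures.** None is given for these outcomes. The sample size supplies the group size and reproduces.
- Primary: 2 × (1.96 + 0.842)² × 1.6² / 1.25² = 25.7, so 26 per group by the normal formula. The t test gives 26.7, so 27 (power 80.4%).
- Per phenotype: (30 + 15) / (1 − 1/6) = 54, of whom 54 × 2/3 = 36 receive lacosamide. With 1/6 lost, 36 × 5/6 = 30 remain. I use 30 v 30 lacosamide patients.

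**Assumptions, none in the documents.** The sign is present in a share p₁ of irritable and p₂ of non-irritable patients. Evoked pain T has mean μ = 5 and SD 2 if the sign is present, and is 0 if absent. Measurement noise has SD 1 at each visit. Everyone has the same proportional fall r, so there is no phenotype-specific effect on that scale.

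**Formula.** For a patient with the sign, change = rT + e with Var(e) = 1 + 1 = 2; otherwise change = 0. Ignoring rounding and clipping:
- difference in mean change D = r μ (p₁ − p₂)
- variance in a group V(p) = p[r²(μ² + SD²) + 2] − (p r μ)²
- SE = √[(V(p₁) + V(p₂))/30], and the rejection rate is about P(Z > 1.96 − D/SE)

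Example, r = 0.3 and 60 v 40%:
- r²(25 + 4) + 2 = 4.61
- V(0.6) = 2.766 − 0.810 = 1.956; V(0.4) = 1.844 − 0.360 = 1.484
- SE = √(3.440/30) = 0.339; D = 0.3 × 5 × 0.2 = 0.30; D/SE = 0.89
- rejection rate about 14%

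Simulation with ratings rounded and clipped to 0–10 (1,500 runs per setting), r = 0.3:

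| Sign, irritable v non-irritable | D (NRS) | Formula | t test | Mann–Whitney |
|---|---|---|---|---|
| 60 v 40% | 0.30 | 14% | 13% | 15% |
| 70 v 30% | 0.60 | 44% | 43% | 49% |
| 80 v 30% | 0.75 | 60% | 58% | 66% |
| 90 v 30% | 0.90 | 75% | 71% | 79% |
| 90 v 10% | 1.20 | 98% | 96% | 98% |

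**Sensitivity to the assumptions.**
- Mean 4.5 instead of 5, 30% fall: about 13% (t test) and 15% (Mann–Whitney) at 60 v 40%, rising to about 82% and 86% at 90 v 20%. There D = 0.3 × 4.5 × 0.7 = 0.95.
- Mean 4.5, 15% fall, 90 v 50% to 90 v 20%: 13–37% (t test), 16–41% (Mann–Whitney).
- No shared fall: 4–6% (t test), 6–9% (Mann–Whitney).
- Equal prevalence, 50 v 50%: 5–6%.
- Visit-3 values compared instead of change (Mann–Whitney): 28–100% across the unequal-prevalence settings, even with no fall in anyone.

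**Alternatives.**
- Lacosamide v placebo within one phenotype (36 v 18, sign in 80%, same 30% fall in both arms): 4.6%, with no adjustment.
- Irritable v non-irritable with the visit-2 value as covariate, 30–50% shared fall: 4–7% at 60 v 40% and 70 v 30%, 8–14% at 80 v 30% and 90 v 30%, 17–20% at 90 v 10%. With no fall at 90 v 10% it is 28%. Adjustment alone does not rescue this contrast when baselines hardly overlap.
- Irritable v non-irritable restricted to patients with the sign at visit 2: about 4–6% of testable runs. At 90 v 10% only about 57% of runs had enough non-irritable patients (0.031/0.57 = 5.4% of those rejected).

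**The case against.** The other side has substantial points.

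- **Contrast.** A reader might infer that the article plans to test these outcomes irritable v non-irritable. It does not say so. It fixes that contrast for average pain only, and the contrast for tertiary outcomes may properly be left to the full protocol or SAP. If only lacosamide v placebo within phenotype is intended, the artefact disappears.
- **Phenotype.** A reader might infer that the groups were formed on sensory gain. The definition is withheld; the description of QST and the exploratory objectives point that way but do not establish it.
- **Covariate sentence.** It concerns baseline pain intensity and centre. It would be wrong to say that the authors claim equal evoked pain at baseline. What stands is that the only reason offered for unadjusted tests does not reach these outcomes.
- **Floor.** A reader might apply the floor at zero to all four measures. It is clearest for brush and cold allodynia. The pinprick score is a difference and can be negative, so only the baseline-imbalance part applies. Nothing in the article says that non-irritable patients score 0 for hyperpathia.
- **Scale.** With an equal proportional fall, mean absolute changes really do differ, so the t test rejects a false null. The rates above are errors only if the result is read as a phenotype-specific response, which is the biomarker reading at issue.
- **Safeguard.** The article already says that the placebo comparison is needed to justify a predictive biomarker. This limits the harm and points to the remedy.

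**Conclusion.** The point holds conditionally and is minor. Unadjusted tests are assigned to the evoked-pain outcomes, and the reason given cannot be carried over to them if sensory gain helps define the phenotype. If they are then compared between phenotypes on change, a shared decline creates a difference: roughly 13–85% of trials significant at a 30% fall for prevalences from 60 v 40% to 90 v 20%, more under greater separation, and near nominal with no shared fall or equal prevalence. Prevalence, mean, SD, noise and fall are all assumed, so the range shows sensitivity and is not a forecast. The documents do not support a claim that the trial will produce a false biomarker finding. The primary outcome is not touched.

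**What to change.** For brush and cold allodynia, pinprick hyperalgesia and hyperpathia:

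1. State that inference rests on lacosamide v placebo within each phenotype, the contrast of the supportive objective, with the visit-2 value as covariate. Randomisation protects this comparison, and the covariate mainly serves precision.
2. Report visit-2 and visit-3 values and the share of patients with the sign by phenotype, descriptively.
3. State that an unadjusted irritable v non-irritable difference in change will not be cited as biomarker evidence.
4. Keep an analysis limited to patients with the sign at visit 2 as a sensitivity analysis only. At an assumed 20% prevalence among non-irritable patients, 30 + 15 evaluable patients leave about 0.2 × 30 = 6 on lacosamide and 0.2 × 15 = 3 on placebo.

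The cost is a few sentences in the SAP; visit-2 values are already collected. The price is that the within-phenotype comparison will have little power in the non-irritable group if the signs are rare there.
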